#### Participant recruitment

Recruitment of participants will be conducted from 28 weeks gestation and survey collection will occur from 32 weeks gestation with care to recruit young and marginalised women to prevent under-sampling.

Staff at the participating sites will offer the woman a show bag containing information about the project, giveaways (as determined by staff at the site, funded by the project), and the Participant Information Statement PIS). Staff will ask verbal permission from the participant to pass on their mobile phone number (landline and/or email) to the research team so they may to be contacted regarding the study.

Staff at the sites will record the potential participant’s name on a log that contains the woman’s name, mobile number, and Estimated Due Date (EDD). This information will be scanned by the staff member and emailed or faxed to the research team, weekly.

All participants will be provided with a $50 gift card at the six-week interview (6 weeks post-birth) as an incentive for participating in the project. Those who do not have a mobile phone can be provided with one as part of the project.

#### Randomisation of Sites

The study design involves simple cluster randomisation so that sites will be randomised and stratified according to rurality (using the Modified Monash Model (MMM)). We recruited interested maternal and child health services from all over NSW with more than 50 births per year. Stratified randomisation is key to avoiding potential for unbalanced factors between arms to maintain comparability or control for random variability. Randomisation will stratify by the MMM – MM1 (major city) through to MM3 (large rural towns) using a computer-based program by a biostatistician.

#### Consent

Participants will be provided with written information about the project - the Participant Information Sheet (PIS) - contained in the show bag offered by site staff. Consent will be provided over the phone (for phone survey collection) or via implied consent (emailed survey or survey link sent by SMS). For participants between 14 and 17 years old, additional consent will be sought from a parent or guardian (audio-recorded verbal consent at the commencement of the project).

#### Data collection

A research assistant or associate research fellow will collect data. The research team will call potential participants that have provided their contact details. They will again be verbally given information about the project, from the PIS and will be asked to provide verbal consent. Surveys will be collected at these time-points (see Fig. 2):

Baseline (32–40 weeks of gestation).6 weeks post-birth (after which a $50 voucher will be sent to participant).4 months post-birth.6 months post-birth.12 months post-birth (SMS message).

If participants are not contactable by telephone after three attempts, a link to the survey will be emailed to them or sent via SMS (to a maximum of three times over three weeks). Permission will also be requested for the maternal and child health team to inform peer workers when the women have given birth to their babies, in order to ensure early access to the intervention.

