#### Intervention

##### Peer support workers will be employed three days a week for three years in three communities

We plan an **evidence-based, culturally appropriate and best practice intervention** designed with the aim to improve the initiation of breastfeeding and support the continuation of exclusive breastfeeding to best practice standards. Following the systematic review of the evidence the intervention will include:

Employment of Aboriginal breastfeeding peer support workers, who community mentor training, provided through the ABA. Trained Aboriginal peer support workers will then be hosted by maternal and child services in three sites randomised to receive the intervention.

The intervention group will receive scheduled breastfeeding Aboriginal peer breastfeeding support at an antenatal visit, then again within the first week after birth and then support over the following 6 months. The peer workers will provide support such as weekly telephone calls and/or SMS text messages for 6 weeks after birth, along with face-to-face visits where possible (for example clinic visits, mothers’ group or home visits when accompanying other staff). As appropriate, video-chats will be included, as part of a program of monthly Aboriginal peer worker video-chats (via smart-phone video) about breastfeeding. Opportunistic support will also be provided for emerging issues, for example nipple pain. If required, breastfeeding technical support will be sought by the Aboriginal peer support workers from experienced midwives, Aboriginal Health Workers (AHWs), Aboriginal Health Practitioners, ABA counsellors or lactation consultants, or women would be referred to these health care professionals for medical support (such as support for mastitis). Our team will offer cultural safety training for ABA peer counsellors and lactation consultants where appropriate, to ensure they can provide local, culturally appropriate/informed technical support for the Aboriginal peer workers and women.

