#### Analysis

Data from telephone/email surveys at baseline prior to birth, 6 weeks, 4 months and 6 months will be entered into a matrix in REDCap ©, an electronic data collection program by the research team. This data will be collated into Excel, cleaned and analysed, with supervision by the biostatistician. Data will be coded, Statistician and Health Economist will remain blinded throughout the length of the study.

Peer worker interactions with participants will be logged, along with notes about factors which might affect uptake (i.e. participants not available to respond, other priorities such as funerals) so as to undertake process analysis, in addition to outcome analysis. This will be scanned/emailed to the research team for analysis.Interactions with participants will be logged by peer workers (on paper/electronic, stored in a locked secure environment at the site, then emailed or scanned to the research team and entered into REDCap©) to ensure scheduled visits had occurred, and to record any issues that could be incorporated into a process analysis (e.g. participant did not respond, participant had moved).We will use ‘journal’ reflective practice data for analysis of Aboriginal peer workers’ interactions [24].

We plan to recruit at least 360 participants and 306 participants completing 6 weeks in both of group 1 (intervention) and group 2 (control), with three sites in each group (120 participants and 102 completing 6 weeks per site assuming 15% drop out) providing 80.1% power to detect a difference between the group proportions of 0.1500. The proportion in group 1 (the treatment group) is assumed to be 0.2500 under the null hypothesis and 0.4000 under the alternative hypothesis. The proportion in group 2 (the control group) is 0.2500. The test statistic used is the two-sided Z-Test (Pooled), the intra-cluster correlation is 0.0100 and the significance level of the test is 0.050.

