Demographic and risk data including Estimated Due Date (EDD), age, pre/post-pregnancy weight/height (BMI) (at baseline, and weight at six months, self-reported), smoking status (at baseline and 6 months, self-reported), educational level, employment after birth and socioeconomic status (as obesity, low education, low socioeconomic status and returning to work are associated with decreased breastfeeding). We will also ask about previous breastfeeding experience and parity.

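### Women appear to be approached and consented after site allocation, with no stated rule that consent and baseline precede the antenatal peer visit, so who enrols can differ by arm unnoticed

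*Protocol article*

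**What the plan says.** - **Allocation.** In Randomisation of Sites, "sites will be randomised and stratified according to rurality". The Analysis section gives three sites per arm.
- **Approach.** Under Participant recruitment, staff of the participating sites hand out study information from 28 weeks, ask permission to pass on contact details, and keep a log of each potential participant's name, mobile number and due date. The same section says "survey collection will occur from 32 weeks gestation with care to recruit young and marginalised women to prevent under-sampling". It gives no rule for consecutive approach.
- **Consent and baseline.** Under Consent and Data collection, the research team takes verbal consent by phone, or consent is implied by completing an emailed or texted survey. If calls fail, links are sent up to three times over three weeks. The first survey is listed as "Baseline (32–40 weeks of gestation".
- **Intervention.** Peer workers are hosted at three sites for three years. "The intervention group will receive scheduled breastfeeding Aboriginal peer breastfeeding support at an antenatal visit", with further support after birth. The text gives no gestational age for that visit and no order relative to consent or the baseline survey.
- **Enrolment rate.** The Analysis section aims for 40 women per site per year for three years, out of roughly 80–100 births per year.
- **Blinding.** The Analysis section names the statistician and health economist as blinded. It does not name site staff or interviewers.
- **Covariates.** Demographic and risk data are collected, and "We will also ask about previous breastfeeding experience and parity".

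**The concern.** Cluster randomisation makes the sites comparable in expectation. It makes the enrolled women comparable only if identification and consent do not depend on the site's arm. Here the people who approach women work at the randomised services, and at three of those services a peer worker is part of the team. Two routes to a difference in case mix follow.

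1. **Approach.** Staff who can offer peer support may mention the study to different women, or present it differently, from staff who can offer only usual care.
2. **Consent.** An intervention woman may meet the peer worker before she decides whether to take part. A control woman cannot.

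The bias could run either way. Women keen to breastfeed may join more readily where support is on offer, or staff may steer women expecting difficulty towards it. Either would be mixed into the primary comparison of exclusive breastfeeding. The log would not show it, because it does not record how many women were eligible, approached or declined.

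**Working it through.** **1. Timing, from the text.** No sentence says that allocation precedes enrolment. Peer employment (three years) and enrolment (40 per site per year for three years) have the same length, and intervention women must have a peer worker in post. The periods must therefore largely overlap, and most women are probably approached with allocation visible. This is an inference.

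**2. Order of consent and first peer contact.** Approach opens at 28 weeks, and consent and baseline fall at 32–40 weeks. This leaves at least 32 − 28 = 4 weeks between the earliest approach and the earliest survey, and up to 40 − 28 = 12 weeks to the latest. The antenatal peer visit has no date, so the prose allows it on either side of consent.

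**3. Room for selection.** 40/100 = 40% to 40/80 = 50% of births per site-year are to be enrolled. At a site near the entry threshold of 50 births per year, the share would be close to 40/50 = 80%, with less room.

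**4. The plan's own power figure.** Inputs from the Analysis section: 102 analysed per site, three sites per arm, ICC 0.01, 25% versus 40%, two-sided pooled Z-test, alpha 0.05.
- Design effect = 1 + (102 − 1) × 0.01 = 2.01.
- Effective n per arm = 306 / 2.01 = 152.2.
- Standard error under the null = √(2 × 0.325 × 0.675 / 152.2) = 0.0537. Under the alternative it is √((0.40 × 0.60 + 0.25 × 0.75) / 152.2) = 0.0530.
- Power = Φ((0.15 − 1.96 × 0.0537) / 0.0530) = 80.1%.

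The article reports "providing 80.1% power to detect a difference between the group proportions of 0.1500", so its figure reproduces. The calculation takes the women in the two arms to be comparable and leaves no allowance for differential enrolment.

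**5. Illustration of size (assumed values, not in the documents).** Suppose women inclined to breastfeed have exclusive breastfeeding at 6 weeks 20 to 30 points higher than others, and their share among those enrolled differs between arms by 10 to 20 points. The spurious difference is b = (difference in share) × (gap in outcome). With no true effect, p₂ = 0.25 and p₁ = 0.25 + b. The two-sided rejection rate is Φ((b − 1.96 s₀)/s₁) + Φ((−b − 1.96 s₀)/s₁). Here s₀ and s₁ are the pooled and unpooled standard errors at effective n 152.2.

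| Share difference | Outcome gap | b | b / 15 points | Rejection rate |
|---|---|---|---|---|
| 0 | any | 0 | 0% | 5% |
| 10 points | 20 points | 2 points | 13% | 6.8% |
| 10 points | 30 points | 3 points | 20% | 9.1% |
| 20 points | 20 points | 4 points | 27% | 12.3% |
| 20 points | 30 points | 6 points | 40% | 21.4% |

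For the last row: s₀ = √(2 × 0.28 × 0.72 / 152.2) = 0.0515 and s₁ = √((0.31 × 0.69 + 0.25 × 0.75) / 152.2) = 0.0513. This gives 0.213 + 0.001 = 0.214.

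**The case against.** **Missing figures.** The article refers to Figure 1 for the schedule of enrolment, intervention and data collection and to Figure 2 for the flowchart, and neither is shown. Either may place baseline before the antenatal visit. This stands: the gap is in the prose, and the first request is to state the order. Data collection also seeks permission to tell peer workers of births just after describing consent, which suggests that postnatal contact follows consent. Only the antenatal visit is left unordered.

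**Site staff are not said to select.** The text says that they offer information, and the research team takes consent. That is fair. Nothing describes deliberate selection, but nothing requires consecutive approach either, and those who approach women are not named as blinded.

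**The magnitude is assumed.** This also stands. The table shows what differential enrolment would do, and does not show that it will occur.

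A reader might also infer four stronger points that the documents do not support:

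- *That the primary comparison is unadjusted.* The pooled Z-test appears only in the power statement. Prognostic variables are collected, and a statistical analysis plan that is not shown may specify adjustment.
- *That the baseline data are contaminated and unusable.* A peer visit cannot change parity or previous breastfeeding, and can scarcely change education. For these the issue is who enrols. Only changeable answers, such as self-reported smoking, could be affected by contact.
- *That variables measured after allocation will be adjusted for.* Employment after birth and six-month smoking and weight are listed as data collected. No model is stated.
- *That the small number of sites causes the problem.* Differential recruitment is systematic, and more sites would not remove it.

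**Conclusion.** The concern holds as a weakness in the enrolment procedure. Followed as written, the procedure lets approach and consent depend on allocation, and the log could not show whether they did. An analysis plan cannot repair this later, because it cannot recover counts that were never recorded or change who was enrolled.

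The conclusion rests on two readings: that allocation precedes most enrolment, inferred from the matching three-year periods, and that the missing figures do not already place consent and baseline before the peer visit. The size is not known. Under the assumed range, the spurious difference is 2 to 6 points against a 15-point target, and the false-positive rate of the stated test is about 7–21% instead of 5%. The 80.1% power figure is correct on its own inputs. No particular method of primary analysis follows from this point.

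**What to change.** 1. State the order of allocation, approach, consent, baseline survey and first peer contact. Obtain consent and complete the baseline survey before the first study contact with the peer worker.
2. At all six sites, offer enrolment consecutively to eligible women. Extend the existing log with anonymous counts of women eligible, approached, referred and consented, and report them by arm.
3. As a recommendation only, since an analysis plan may already cover it: adjust the primary comparison for pre-allocation characteristics already collected (parity or previous breastfeeding, education). Do not adjust for employment after birth or for six-month smoking and weight.

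**Cost.** Baseline calls must be booked earlier at intervention sites, and all sites have slightly more logging. Anonymous counts avoid holding identifying details of women who have not agreed to be contacted.

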**Fig. 2 Fig2:**
[figure not shown]
RCT Flowchart

#### Intervention

##### Peer support workers will be employed three days a week for three years in three communities

We plan an **evidence-based, culturally appropriate and best practice intervention** designed with the aim to improve the initiation of breastfeeding and support the continuation of exclusive breastfeeding to best practice standards. Following the systematic review of the evidence the intervention will include:

Employment of Aboriginal breastfeeding peer support workers, who community mentor training, provided through the ABA. Trained Aboriginal peer support workers will then be hosted by maternal and child services in three sites randomised to receive the intervention.

The intervention group will receive scheduled breastfeeding Aboriginal peer breastfeeding support at an antenatal visit, then again within the first week after birth and then support over the following 6 months. The peer workers will provide support such as weekly telephone calls and/or SMS text messages for 6 weeks after birth, along with face-to-face visits where possible (for example clinic visits, mothers’ group or home visits when accompanying other staff). As appropriate, video-chats will be included, as part of a program of monthly Aboriginal peer worker video-chats (via smart-phone video) about breastfeeding. Opportunistic support will also be provided for emerging issues, for example nipple pain. If required, breastfeeding technical support will be sought by the Aboriginal peer support workers from experienced midwives, Aboriginal Health Workers (AHWs), Aboriginal Health Practitioners, ABA counsellors or lactation consultants, or women would be referred to these health care professionals for medical support (such as support for mastitis). Our team will offer cultural safety training for ABA peer counsellors and lactation consultants where appropriate, to ensure they can provide local, culturally appropriate/informed technical support for the Aboriginal peer workers and women.

#### Control

Normal/usual antenatal and postnatal care in three communities.

All sites will receive usual lactation support, including advice from midwives and AHW in antenatal programs, early childhood nurses and AHW, advice from midwives, junior doctors and paediatricians in hospital maternity wards, and from lactation consultants based in hospitals. Other lactation support is provided by general practitioners (for example in Aboriginal medical services), child health nurses and community lactation consultants on demand or during routine postnatal checks and immunisation reviews. Some Aboriginal women also may access private lactation consultants or access the ABA hotline.

#### Analysis

Data from telephone/email surveys at baseline prior to birth, 6 weeks, 4 months and 6 months will be entered into a matrix in REDCap ©, an electronic data collection program by the research team. This data will be collated into Excel, cleaned and analysed, with supervision by the biostatistician. Data will be coded, Statistician and Health Economist will remain blinded throughout the length of the study.

Peer worker interactions with participants will be logged, along with notes about factors which might affect uptake (i.e. participants not available to respond, other priorities such as funerals) so as to undertake process analysis, in addition to outcome analysis. This will be scanned/emailed to the research team for analysis.Interactions with participants will be logged by peer workers (on paper/electronic, stored in a locked secure environment at the site, then emailed or scanned to the research team and entered into REDCap©) to ensure scheduled visits had occurred, and to record any issues that could be incorporated into a process analysis (e.g. participant did not respond, participant had moved).We will use ‘journal’ reflective practice data for analysis of Aboriginal peer workers’ interactions [24].

We plan to recruit at least 360 participants and 306 participants completing 6 weeks in both of group 1 (intervention) and group 2 (control), with three sites in each group (120 participants and 102 completing 6 weeks per site assuming 15% drop out) providing 80.1% power to detect a difference between the group proportions of 0.1500. The proportion in group 1 (the treatment group) is assumed to be 0.2500 under the null hypothesis and 0.4000 under the alternative hypothesis. The proportion in group 2 (the control group) is 0.2500. The test statistic used is the two-sided Z-Test (Pooled), the intra-cluster correlation is 0.0100 and the significance level of the test is 0.050.

At 6 weeks we expect a prevalence of exclusive breastfeeding to be 25% in the control group, based on breastfeeding prevalence of 26% seen at 6 weeks in the Gudaga study (Craig et al., 2011) while if effective we estimate prevalence of exclusive breastfeeding in the intervention group to be 40% or more. A Cochrane review by McFadden et al. [18] reported women in intervention groups were less likely to stop exclusive breastfeeding by 6 weeks (RR 0.79, 95% CI 0.71 to 0.89)., which applied to a base rate of 75% stopping breastfeeding leads to 15% higher absolute breastfeeding rates at 6 weeks (40% vs. 25%). However, we consider the current study intervention to be more intense than other studies included in that meta-analysis.

Elliot-Rudder [19] conducted a cluster RCT where health professionals were trained in motivational interviewing to support women to continue breastfeeding. In a sample of 330 women, with the outcome of exclusive breastfeeding at 4 months (OR 1.88, 95% CI 1.01–3.6, p = 0.047), this study was able to demonstrate effectiveness of the intervention.

We plan to use survival analysis to assess one of our secondary outcomes (using another outcome, days of exclusive breastfeeding).

We will recruit approximately 120 mother – babies in each of six sites (aiming for 40 per year for 3 years, given approximately 80–100 births per year in each site).

Primary outcomes: (a) Exclusive breastfeeding at 6 weeks (24 h recall telephone questionnaire or via survey email). (b) Exclusive breastfeeding at 4 months (24 h recall telephone or survey email) (c) Exclusive breastfeeding at 6 months (24 h recall telephone or survey email).

Secondary outcomes: (a) Initiation of breastfeeding within first 24 h (self – report, 6 week survey), (b) Days of exclusive breastfeeding (self-report) (c) Days of any breastfeeding (self-report) (d) Age at introduction of expressed breastmilk (self-report). (e) Age introduction of solid/semi-solid food (self-report) (f) Age at introduction of other breastmilk substitutes (self-report) (g) Reason for cessation of breastfeeding including contraindications to breastfeeding (self-report) (h) Hospitalisation in first 6 months of life (self – report at six months) (i) Otitis media requiring antibiotics in first six months of life (self – report at six months). (j) Breastfeeding at 12 months (SMS – yes/ no).

Demographic and risk data including Estimated Due Date (EDD), age, pre/post-pregnancy weight/height (BMI) (at baseline, and weight at six months, self-reported), smoking status (at baseline and 6 months, self-reported), educational level, employment after birth and socioeconomic status (as obesity, low education, low socioeconomic status and returning to work are associated with decreased breastfeeding). We will also ask about previous breastfeeding experience and parity.

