**Methods:**

We will evaluate the effect of scheduled breastfeeding peer support for and by Aboriginal women, on breastfeeding initiation and the prevalence of exclusive breastfeeding. This MRFF (Medical Research Future Fund) funded project is designed as a single-blinded cluster randomised controlled trial recruiting six sites across New South Wales, Australia, with three sites being randomised to employ a peer support worker or undertaking standard care. Forty pregnant women will be recruited each year from each of the six sites and will be surveyed during pregnancy, at six weeks, four and six months postnatally with a single text message at 12 months to ascertain breastfeeding rates. In-depth interviews via an Indigenous style of conversation and storytelling called ‘Yarning’ will be completed at pre- and post-intervention with five randomly recruited community members and five health professionals at each site” [5]. Yarns will be audio recorded, transcribed, coded and thematic analysis undertaken. Health economic analysis will be completed to assess the health system incremental cost and effects of the breastfeeding intervention relative to usual care.

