#### Sample size

We plan to recruit a total of 720 participants (120 at each site), allowing for a predicted 15% drop out at 6 months post-birth, resulting in 612 participants for analyses.

A similar intervention, the RUBY Study (Forster et al., 2017) was able to follow-up 88% of participants so we believe a 15% drop-out rate is likely conservative.

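### The 80.1% power rests on a normal Z-test with only three sites per arm; on the 4 degrees of freedom the design provides, power is about 57%

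*Protocol article*

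**What the plan says.** The site is the unit of randomisation. The Randomisation of Sites section states: "The study design involves simple cluster randomisation so that sites will be randomised and stratified according to rurality". The Analysis section of the RCT gives the size of each arm, "We plan to recruit at least 360 participants and 306 participants completing 6 weeks in both of group 1 (intervention) and group 2 (control"), and its make-up, "with three sites in each group (120 participants and 102 completing 6 weeks per site assuming 15% drop out"). It describes this sample as "providing 80.1% power to detect a difference between the group proportions of 0.1500". The control proportion is 0.25 and the intervention proportion under the alternative is 0.40. The test and the clustering assumption follow in one sentence: "The test statistic used is the two-sided Z-Test (Pooled), the intra-cluster correlation is 0.0100 and the significance level of the test is 0.050".

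The ICC appears as a single value, with no source and no range. The article makes no small-sample allowance for having six clusters, and it names no other test or model for the primary outcomes.

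**The concern.** The calculation inflates the variance for clustering but keeps the normal critical value. That is sound when there are many clusters, or when the ICC is truly known. Here there are six clusters, and a valid analysis has to learn the between-site variance from them. Two site means per arm beyond the arm mean give 2 × (3 − 1) = 4 degrees of freedom, and the t critical value of 2.776 is much larger than 1.96.

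Two things are at stake:

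- If the final analysis uses a valid small-cluster method, the trial does not have the power it states. A null result would invite the reading that peer support does not work, when the trial had little better than an even chance of detecting the planned benefit.
- If the Z-test is carried into the analysis, the type I error can be well above 5%.

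**Working it through.** **Inputs (Analysis section).** Three sites per arm; 102 completers per site, so 306 per arm; proportions 0.40 and 0.25; ICC 0.01; two-sided alpha 0.05.

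**Step 1: reproduce the stated power.**

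- Design effect = 1 + (102 − 1) × 0.01 = 2.01.
- Effective n per arm = 306 / 2.01 = 152.2.
- Mean proportion = (0.40 + 0.25) / 2 = 0.325.
- Pooled SE = √(2 × 0.325 × 0.675 / 152.2) = 0.0537.
- Unpooled SE = √((0.40 × 0.60 + 0.25 × 0.75) / 152.2) = √(0.4275 / 152.2) = 0.0530.
- Power = Φ((0.15 − 1.96 × 0.0537) / 0.0530) = Φ(0.845) = 80.1%.

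This matches the protocol, so the method is identified: a design effect followed by a normal critical value.

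**Step 2: same inputs, t reference on 4 degrees of freedom.**

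- Degrees of freedom = 6 − 2 = 4; critical value 2.776.
- Noncentrality = 0.15 / 0.0530 = 2.83.
- Noncentral-t power = 57.2% (56.2% with the pooled SE).

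A beta-binomial simulation of 200,000 trials (three sites of 102 per arm, ICC 0.01), analysed by a t-test on site proportions, gave 57.2% power and 5.0% type I error.

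**Step 3: difference detectable with 80% power.** For 45% versus 25% the SE is √((0.2475 + 0.1875) / 152.2) = 0.0535. The noncentrality is 0.20 / 0.0535 = 3.74 and power is 79.6%. The detectable difference is therefore about 20 points, not 15.

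**Step 4: sensitivity to the ICC.** Only 0.01 is in the protocol; the other values are assumptions.

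| ICC | Design effect | Effective n per arm | Z power | t (4 df) power |
|---|---|---|---|---|
| 0.005 | 1.505 | 203.3 | 90% | 69% |
| 0.01 | 2.01 | 152.2 | 80.1% | 57% |
| 0.02 | 3.02 | 101.3 | 63% | 42% |
| 0.05 | 6.05 | 50.6 | 36% | 24% |

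**Step 5: type I error if 1.96 is kept.** The result depends on how the Z statistic is formed, which the protocol does not say.

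- Site-level variance estimated from the data: P(|t₄| > 1.96) = 12.2%, with about 79% power.
- Variance fixed at ICC 0.01 when the true ICC is 0.02 (assumed): 2 × (1 − Φ(1.96 / √(3.02 / 2.01))) = 11%.
- Plain pooled Z ignoring clustering, true ICC 0.01: 2 × (1 − Φ(1.96 / √2.01)) = about 17%.
- Variance fixed at ICC 0.01 and the true ICC exactly 0.01: 5.0%, with about 80% power.

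**Step 6: effect of stratification.** The 4 degrees of freedom ignore the rurality strata. If one stratum term is fitted, 3 remain and power is about 47–49%. An unrestricted 3:3 allocation has 20 arrangements, so a two-sided permutation p-value cannot fall below 2/20 = 0.10. Stratification leaves fewer arrangements, so the floor is no lower.

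**The case against.** The strongest reply is that 80.1% is not a miscalculation. It follows exactly from the stated inputs, and a Z-test with the ICC fixed at its true value does hold 5% error with about 80% power. That is correct: the fault is in the reference distribution, and the 57% keeps the plan's effect, sample and ICC while replacing its test. The defence requires the ICC to be known to be 0.01, and the article offers no support for that.

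A second reply is that the Z-test sentence lists sample-size inputs, while the analysis model belongs in a statistical analysis plan that is not shown. This stands in part. The type I error figures are conditional on the Z-test being carried forward, and the article does not say outright that it will be. The power statement gains nothing from this reply, however. If the analysis plan names a valid small-cluster method, the 80.1% is not the power of that method.

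A third reply is that assumed ICCs above 0.01 show only one direction. That is fair, and 0.005 is therefore tabulated. Even there, power on 4 degrees of freedom is 69%, below the claim.

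Finally, restating the power does not make the trial better powered. That is true. With 102 completers per site and ICC 0.01, four sites per arm would give 77.7% and five 89.1%. If six sites is the practical limit, the power should still be reported as it is.

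**Conclusion.** The concern holds. On the protocol's own proportions, site size and ICC, a test that estimates between-site variance and keeps a 5% error rate has about 57% power, roughly 23 points below the 80.1% stated. A true 15-point benefit would be missed about 43% of the time. The figure assumes equal sites of 102, a true ICC of 0.01 and no degrees of freedom spent on strata. Fitting the rurality strata or a larger ICC would lower it; a smaller ICC would raise it, to 69% at 0.005. The stated power is attainable at 5% error only if the ICC is treated as known.

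**What to change.** 1. In the Analysis section, restate the power on 4 degrees of freedom: about 57% for 25% versus 40%, or about 80% for 25% versus 45%, at ICC 0.01. Give values for other ICCs such as 0.02 and 0.05, labelled as assumptions, and say whether rurality strata will be fitted.
2. Replace the pooled Z-test with a t-test on the six site summaries (4 degrees of freedom), or a mixed model or GEE with a small-sample correction and between-cluster degrees of freedom. Use the same method in the analysis plan.
3. Make the estimated difference with its t-based confidence interval the headline result, so that a non-significant finding is read with its uncertainty.

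The cost is wording in the protocol and the analysis plan. No extra participants are needed, but the stated power becomes less favourable.
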